## Abstract

**Background:**

Research on physical activity and nutrition interventions aimed at positively impacting symptom management, treatment-related recovery and quality of life has largely excluded head and neck (HN) cancer populations. This translates into a lack of clinical programming available for these patient populations. HN cancer patients deal with severe weight loss, with more than 70% attributed to lean muscle wasting, leading to extended recovery times, decreased quality of life (QoL), and impaired physical functioning. To date, interventions to address body composition issues have focused solely on diet, despite findings that nutritional therapy alone is insufficient to mitigate changes. A combined physical activity and nutrition intervention, that also incorporates important educational components known to positively impact behaviour change, is warranted for this population. Our pilot work suggests that there is large patient demand and clinic support from the health care professionals for a comprehensive program.

**Methods/Design:**

Therefore, the purpose of the present study is to examine the impact and timing of a 12-week PA and nutrition intervention (either during or following treatment) for HN cancer patients on body composition, recovery, serum inflammatory markers and quality of life. In addition, we will examine the impact of a 12-week maintenance program, delivered immediately following the intervention, on adherence, patient-reported outcomes (i.e., management of both physical and psychosocial treatment-related symptoms and side-effects), as well as return to work.

**Discussion:**

This research will facilitate advancements in patient wellness, survivorship, and autonomy, and carve the path for a physical-activity and wellness-education model that can be implemented in other cancer centers.

**Trial registration:**

Current Controlled Trials NCT01681654

## Background

Head and neck (HN) cancers include cancers of the lip, oral cavity, oropharynx, hypopharynx, tonsil, salivary glands, nasopharynx, nose paranasal sinus, and middle ear
[1]. They are the sixth most common cancer worldwide
[2]. HN cancers account for approximately 3% of all cancers in the United States and are nearly twice as common among men as they are among women
[1]. In 2011, approximately 52,000 people in the United States were diagnosed with HN cancers and over 5000 in Canada, and the 5-year survival rate is currently at 57%
[1,3]. Advances in medical detection and interventions are helping to increase 5-year overall cancer survival rates, leading to an ever-growing number of cancer survivors
[4]. Since the long-lasting effects of the disease and treatments may impact all survivors, the focus on survivorship care and patient outcomes is paramount
[5].

There is persuasive evidence to suggest that two lifestyle behaviors, physical activity (PA) and nutrition are necessary components in cancer survivorship programming
[6]. PA has been shown to enhance patient functional capacity, physical functioning, and body composition, as well as facilitate the management of treatment related symptoms and side-effects including fatigue, and nausea
[7-11]. Nutritional counseling has been found to improve dietary intake in patients who face increased risk of malnutrition, thereby improving outcomes and timely healing
[12,13]. It is well established that PA and nutrition interventions also promote improved quality of life (QoL) in cancer survivors, regardless of tumour site. To date, the vast majority of lifestyle interventions have focused their attention on breast cancer
[12,14-16]. This has left other cancer populations drastically underserved, including HN cancer survivors, who are at significant risk of long-term disability
[17].

While HN cancer patients face issues similar to other cancer survivor populations (i.e., fatigue, distress, physical functioning), these populations also experience further physical and psychological burden into survivorship, affecting overall QoL status, rehabilitation, and return to work
[17-21]. HN cancer patients deal with severe weight loss, with upwards of 70% attributed to lean muscle wasting, leading to decreased physical functioning with regards to locomotion, strength and respiration after treatment
[19,22]. This cancer-related skeletal muscle wasting, or cachexia, exists due to imbalances between muscle protein synthesis and degradation, and is unique from starvation in the sense that it cannot be reversed or treated solely with nutritional supplementation
[23]. Cachexia is defined as an unintentional weight loss of at least 5% premorbid weight occurring over 3 to 6 months and will be the main cause of death for 20-40% of HN cancer patients, a group especially challenged with this syndrome
[23,24].

Current interventions are largely focused on nutrition, despite findings indicating that decreased food intake is probably not directly related to this muscle wasting, and that dietary intervention alone may increase fat mass without affecting muscle tissue
[25]. Couch et al. (2007) also reported that although nutritional therapy is necessary, alone it might be insufficient, prompting additional or complementary treatment options
[24]. At present there is a lack of complementary treatment options to help sustain or rebuild this wasted muscle, yet since cachexia is a muscle wasting disease, interventions targeted at increasing protein anabolism and decreasing catabolism are warranted
[26]. Strength training and exercise hold great potential due to the associated increases in lean muscle mass and improvements in body composition, which have been seen in other cancer populations
[8,27]. Currently, there are very few clinical trials that examine the impact of strength training in combination with a nutritional intervention for cachexia. Besides the negative impact on overall health and survival, this muscle wasting syndrome is associated with substantial mental and emotional fatigue, and significantly decreased QoL, particularly in scores of emotional, physical and social functioning categories
[18,23,24,28,29]. Exercise and diet have been found to enhance QoL in HN survivors and help manage fatigue, but the specific benefits of a lifestyle intervention during treatment has yet to be investigated, and the question pertaining to the appropriate time of intervention, during treatment or following treatment, has yet to be answered
[17,30].

The purpose of this proposed research is to examine the immediate and long term physical and psychosocial benefits of a clinic-supported physical activity and nutrition program during and after treatment for HN cancer survivors, and to investigate the clinical implications associated with increasing the promotion of healthy lifestyle behaviors for this population. This research will address the pressing need for clinic-supported HN cancer lifestyle interventions that effectively demonstrate physical and psychosocial patient benefit.

Specifically, this study is designed to examine the potential benefits of a lifestyle (PA, nutrition, and health education) intervention. Specific objectives include the following:

1. Whether a lifestyle intervention will improve outcomes, including physiological (muscle mass maintenance), fitness, psychological (QoL and depression), smoking status, inflammatory markers, and functional (return to work).

2. Whether it is optimal, in terms of outcomes, to deliver the program during or after treatment completion.

3. Whether a survivorship care plan (SCP) maintenance program improves long-term healthy lifestyle adherence.

Without exploration into these questions, HN cancer care will continue to only partially serve patients in their quest towards healthy cancer recovery, strong physical functioning ability, improved QoL, and timely return to work. These studies will provide concrete evidence for a clinic-supported lifestyle intervention and maintenance program as a means to mediate these currently unaddressed factors and improve functioning and psychosocial outcomes.

The study hypotheses directly reflect the aims. It is hypothesized that patients who are randomized to the 12-week lifestyle intervention at treatment start will experience improved symptom management throughout treatment compared to controls (delayed intervention) as evaluated by: a) decreased loss of lean body mass, improved physical functioning and fitness outcomes, improved Karnofsky Performance scores and decreased levels of serum inflammatory markers b) improved patient sense of wellbeing and feelings of control and therefore overall reported QoL. It is also hypothesized that patients who are randomized to the 12-week lifestyle intervention at treatment start (immediate intervention) will experience improved symptom management following treatment compared to delayed intervention patients who begin the 12-week intervention following treatment. Improved symptom management will be evaluated following intervention by: a) decreased loss of lean body mass, improved physical functioning and fitness outcomes, improved Karnofsky Performance scores and decreased levels of serum inflammatory markers as well as the associated b) improvement in patient sense of wellbeing, feelings of control, and overall reported QoL score.

## Methods/Design

### Study design

This study will be a randomized controlled trial, with an Immediate Lifestyle Intervention (ILI) group and a Delayed Lifestyle Intervention (DLI) group. The DLI group will act as the control group during the first 12-week phase. Flow through the study is portrayed in Figure 
1. Research ethics approval to conduct this study was obtained through the Conjoint Health Research Ethics Board of the Faculties of Medicine, Nursing and Kinesiology, at the University of Calgary (Ethics ID: E-24446).

**Figure 1 F1:**
[figure not shown]
Study design protocol.

#### Treatment arms

Once enrolled, the participant will be randomized to either begin the intervention at the time of treatment initiation (ILI, n = 40), or to begin the intervention following treatment completion (DLI, n = 40). Patients will be recruited, cleared for participation, receive an initial assessment, and then be randomized into either the ILI group or the DLI group. Participants in the ILI group will receive an individualized exercise and dietary program based on their exercise assessment and dual energy x-ray absorptiometry (DXA) scan results, will attend twice weekly group exercise classes, and perform their individualized at-home program an additional two times per week. In addition, participants will be required to attend six education sessions during the 12-week intervention. The DLI group will receive this intervention upon their treatment completion, at approximately 12-weeks post-randomization.

#### Physical activity intervention

Participants will attend twice weekly exercise classes, for 12 weeks, at the Thrive Centre or Tom Baker Cancer Centre Holy Cross location to practice their program in a supported group-based environment. In addition, participants will receive equipment to perform the program at least two days per week at home. The focus of the PA program will be progressive strength training, helping to rebuild lost muscle mass and prevent further protein degradation. Participants will be asked to perform 8-10 prescribed low-intensity exercises four times per week, conducting approximately 2 sets of 8-10 repetitions. During this time, participants will be asked to record daily activity in a PA log.

#### Dietary intervention

Patients will be screened weekly using the Patient Generated-Subjective Global Assessment tool (PG-SGA) during treatment and will complete a 3-day dietary record at baseline, four weeks, eight weeks, and then at each assessment point thereafter
[31,32]. This information will be scored and a dietitian will review and provide appropriate feedback at weekly dietary counseling sessions.

#### Educational intervention

The educational seminars will focus on providing both nutrition and PA information that will aid in the preparation for behavior change. Specifically, weekly education classes addressing the impact of lifestyle choices on treatment-related symptoms and outcomes, teaching behavior change techniques (goal setting, journaling etc.), and providing time for supportive discussion will be held immediately after an exercise session one time/week.

#### Maintenance intervention

Following the initial intervention, participants in both the immediate and delayed intervention arms will be randomized (20:20 in each group) to either a control (no maintenance program other than access to the workout center) or a 12-week maintenance program immediately following the intervention, consisting of an SCP with both exercise and dietary prescriptions, weekly group-based PA classes, and ongoing monthly education classes.

### Study population

The intervention participants will consist of HN patients who have been newly diagnosed and who have not yet started treatment. Patients will be eligible to participate if they: 1) are over 18 years of age 2) have received a diagnosis of nasopharyngeal, oropharyngeal or hypopharygeal cancer, 3) are scheduled to receive radiation treatment, 4) are able to walk without assistance, 5) have received clearance for exercise from their treating oncologist, 6) live in the Calgary area 7) can speak and write English, and 8) are interested in participating in the program. Reasons for exclusion will be documented as feasibility outcomes of the trial.

### Recruitment

Participants will be recruited through the HN clinic at the Tom Baker Cancer Centre, with direct referral and clearance for exercise from a physician. Once the participant is referred, they will be contacted to discuss the study details and, if interested and meet the inclusion criteria, will receive an appointment time for an initial assessment. At this time, participants will complete a written, informed consent before participation in the study.

### Measures

The assessments will consist of a battery of patient-reported instruments to assess demographics, medical information, PA and dietary behavior, QoL, depression, smoking status as well as a physical fitness assessment and a comprehensive body composition assessment. Inflammatory markers, including TNF, IL-6, IL-1, IL-8 and C-reactive protein will be assessed in serum. A chart review will also be conducted to assess diagnosis, treatment plan and outcomes. The assessment will take approximately 1.5 hours to complete and will occur at baseline (time of diagnosis), 3, 6, 9, and 12-months post diagnosis.

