### Health and lifestyle questionnaires

#### Demographics

Demographics will be collected by self-report including gender, age, ethnicity, marital status, education, employment status, return to work status and annual income. Medical variables, abstracted from chart reviews by study staff, will include specific diagnosis (type, stage, initial or recurrence), time since diagnosis, and current treatment.

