### Health-related fitness assessments

#### Body composition

Standing height and weight will be measured on a Heath Carter balance beam scale. Participants will be weighed weekly during active treatment and during the lifestyle intervention and maintenance phase. Weight will also be tracked at each of the 5 assessments. Waist circumference will be measured with an anthropometric tape measure at the top of the iliac crest and hip circumference will be measured at the greatest girth of the gluteus with the participant standing erect
[42]. Waist to hip ratio and body mass index (kg × m^-2^) will be calculated
[43]. A DXA scan (Hologic QDR 4500; Hologic Inc, Bedford, MA) will be performed a total of five times, at each assessment. Hologic QDR software will be used to determine lean mass, fat mass and bone mineral density. The DXA scans will be done at the Human Performance Laboratory at the University of Calgary.

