### Blood data collection

#### Inflammatory markers

Inflammatory factors will be evaluated as they are associated with cancer cachexia and muscle wasting and may be modified by exercise
[47,48]. An overnight fasted blood draw will be collected at baseline, 3 months post diagnosis, 6 months post diagnosis, 9 months post diagnosis, and 12 months post diagnosis. Once further funding is secured, serum inflammatory cytokine concentrations will be assessed in-house ([name] laboratory) according to our established protocols. TNF, IL-6, IL-1, IL-8 and C-reactive protein will be quantified using Milliplex Human Cytokine kits (Millipore, Billerica, MA). Plate reading will be provided as a fee-for service through Eve Technologies Inc. (Calgary, AB).

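### Assessments are timed from diagnosis but the 12-week phases from treatment start or randomisation, so the 3-month scan precedes the end of the immediate programme for anyone starting treatment more than about 7 days after diagnosis

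*Protocol article*

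**What the plan says.** In the protocol article, the Measures section fixes the timetable for the whole battery: the assessment "will occur at baseline (time of diagnosis), 3, 6, 9, and 12-months post diagnosis". The Inflammatory markers section repeats that clock for blood: "An overnight fasted blood draw will be collected at baseline, 3 months post diagnosis, 6 months post diagnosis", and so on to 12 months. The Body composition section puts the DXA scan on the same timetable; it "will be performed a total of five times, at each assessment".

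The interventions are timed differently. Under Treatment arms, ILI patients "begin the intervention at the time of treatment initiation (ILI, n = 40"), while DLI patients start when treatment is completed, put at roughly 12 weeks from randomisation. Under Study design, DLI serves as control only in the first 12-week phase.

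On the order of events, Treatment arms states: "Patients will be recruited, cleared for participation, receive an initial assessment, and then be randomized". Study population and Recruitment add that patients enter already diagnosed and not yet treated. Physician referral, exercise clearance, contact and a booked appointment all come before the initial assessment, and consent is given at that appointment. The Demographics section lists "time since diagnosis, and current treatment" among the variables taken from the chart.

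**The concern.** The timetable uses three anchors (diagnosis, treatment start and randomisation), and no text shown ties a visit to the end of a phase. Baseline is labelled as the time of diagnosis but cannot literally be then, because referral, clearance and consent come between.

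The 3-month visit carries most of the weight. DLI is untreated by the programme only in the first phase, so this is the one scan that compares programme with no programme on body composition, which the Analysis section names as the primary outcome. If the visit is booked from diagnosis and treatment starts some weeks later, ILI patients are scanned part-way through the programme, at a point that differs between patients. The contrast would then describe a partly delivered programme. A mixed model can use actual visit dates, but it cannot supply an end-of-programme scan that was never taken.

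**Working it through.** **The plan's own figure.** Sample size calculation gives an effect size of 0.63, alpha 0.05, 80% power (printed as beta), 32 per group, and 40 after a 20% buffer. A two-sample t-test with these inputs needs 31.85, so 32, per group one-sided, and 40.5, so 41, two-sided. The stated 32 therefore reproduces one-sided, and 32 / 0.8 = 40. The article does not state sidedness, so both are shown below. The timing point does not depend on it.

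**Slack in the timetable.** One month = 365.25 / 12 = 30.44 days, so 3 months = 91.3 days = 13.04 weeks. The programme lasts 12 weeks = 84 days. Slack = 91.3 − 84 = 7.3 days. Let g be the weeks from diagnosis to treatment start. The ILI programme ends at g + 12 weeks, so it is unfinished at the 3-month scan whenever g > 13.04 − 12 = 1.04 weeks.

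**Later visits.** Take the phases as running back to back, with g also standing for the lag to randomisation in DLI. The second phase (DLI intervention, ILI maintenance) ends at g + 24 weeks. Six months is 26.09 weeks, so it is unfinished when g > 2.1 weeks. DLI maintenance ends at g + 36 weeks. Nine months is 39.13 weeks, so it is unfinished when g > 3.1 weeks.

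**Illustration of dilution.** The article gives no value for g, so a range is assumed. Further assumptions are that every patient in a row has the same lag, that the effect builds up linearly over 12 weeks, and that 0.63 is the full 12-week effect.

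- ILI weeks delivered at 3 months = min(12, 13 − g)
- Effect = 0.63 × weeks / 12
- Power: noncentral t, 32 per group, alpha 0.05

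| Lag g (weeks) | ILI weeks delivered | Effect | Power, one-sided | Power, two-sided |
|---|---|---|---|---|
| 0 or 1 | 12 | 0.63 | 80.2% | 69.9% |
| 2 | 11 | 0.58 | 73.9% | 62.3% |
| 4 | 9 | 0.47 | 58.9% | 46.1% |
| 6 | 7 | 0.37 | 42.4% | 30.4% |
| 8 | 5 | 0.26 | 27.2% | 17.9% |

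For example, at g = 4: 13 − 4 = 9 weeks, and 0.63 × 9 / 12 = 0.47.

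**The case against.** A reader might infer that the 3-month scan does fall before the ILI programme ends. The article does not show this. It gives no lag, and with 7.3 days of slack a patient who starts treatment within a week of diagnosis has finished. Recording time since diagnosis shows that diagnosis and assessment are treated as separate times, but it says nothing about how far apart they are.

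There is also a benign reading. Measures equates baseline with the time of diagnosis, so months post diagnosis may loosely mean months post baseline. Five visits three months apart would then roughly follow consecutive 12-week phases, and the referral steps would fall before time zero. This narrows the problem without removing it: the lag that matters becomes baseline to treatment start, which is also not given, and the same 7-day threshold applies. The diagnosis wording appears in two sections, and staff following it literally would book from diagnosis.

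Figure 1, which portrays study flow, is not shown, and a condensed article may leave visit windows to the full protocol. That is a reason not to claim that no visit can fall at the end of a phase. It does not cure an anchor that the text itself states.

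The power figures are open to fair criticism. They reduce a mixed model of change over time to a t-test at one visit, assume the lag and linear build-up, and use an effect size for which the article gives no time point. They are illustrations only. Finally, both arms share the visit clock, so an inference that the randomised comparison is biased is not supported.

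**Conclusion.** The point holds in conditional form. Visits, including the primary-outcome scan, are anchored to diagnosis, while the phases are anchored to treatment start and to treatment completion or randomisation, and the text shown does not reconcile them. The 3-month scan precedes the end of the ILI programme for any patient whose treatment starts more than about 7 days after diagnosis, or after baseline on the looser reading.

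That threshold rests only on the article's own timings. The consequence for the comparison depends on a lag the article does not give: from no loss at a lag of up to 1 week to the lower rows of the table at several weeks, under the assumptions stated there. What is at stake is dilution of the programme-versus-control contrast. It should be settled before enrolment, because a mistimed scan cannot be recovered.

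**What to change.** - Define baseline as the pre-randomisation assessment, and drop the label that places it at diagnosis.
- In Measures and in Inflammatory markers, replace timing from diagnosis with one anchor common to both arms and tied to the phases, for example the start of cancer treatment. Keep five visits and five scans.
- Schedule the first follow-up (DXA, blood, fitness tests and questionnaires) at the end of the ILI programme. In DLI, schedule it at the matching time and before the first DLI session. Name this visit as the one used for the intervention-versus-control contrast.
- Reconcile the chosen anchor with Treatment arms, which gives the DLI start both as treatment completion and as about 12 weeks from randomisation. If randomisation precedes treatment start, a visit 12 weeks after treatment start could come after DLI has begun, so changing the visit wording alone is not enough. How the DLI start is defined is for the investigators to settle.

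The cost is protocol wording and rebooking of visits. The small downside is that visits no longer fall on round months from diagnosis.
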